**METHODS AND TOOLS:**

The study is an open, randomized, monocentric, comparative prospective study of 2 groups of Parkinson’s patients (the first following a TEP program for 12 months, the second not following this program). We will assess the quality of life of Parkinson’s patients using a specific scale (PDQ-39) and a general scale (SF-36) at 6 and 12 months in 120 Parkinson’s patients (60 in each group). We will also assess the motor condition, psychological condition and social adjustment of the two patient groups. We will gather figures on medical costs using a healthcare consumption notebook indicating the drugs taken, hospitalizations, consultations, etc.

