1. METHODOLOGY
   1. Experimental plan

The study is an open, randomized, monocentric, comparative prospective study of 2 groups of Parkinson’s patients (the first following a therapeutic education program, the second not following this program).

The Parkinson’s patients will be randomly assigned to group I (patients following the therapeutic education program) and group II (patients not following the therapeutic education program).

In both groups, patients will undergo a clinical assessment before randomization and after 6 and 12 months of inclusion. This assessment calls for completing a self-assessment questionnaire that aims to assess quality of life, anxiety, depression and social consequences for these patients. Furthermore, at each visit, neurologists specialized in Parkinson’s disease will carry out a clinical examination notably including a motor assessment. Lastly, at each visit, the patients will give hand in a notebook in which they systematically note each medical consultation (specialized or not) and each hospitalization in order to undertake a medico-economic assessment.

Patients in both groups will undergo regular, conventional follow-ups by their referring neurologist.

[figure not shown]

|  | Visit 1: 1st month | Visit 2: 6th month | Visit 3: 12th month |
| --- | --- | --- | --- |
| Informed consent | X |  |  |
| Randomization | X |  |  |
| Self-assessment questionnaires | X | X | X |
| Clinical examination | X | X | X |
| Filling in the notebook | X | X | X |

We have chosen to carry out a pragmatic study in order to respect the patient’s usual living conditions. We are therefore seeking to interfere as little as possible in the usual care outside the TEP visits.

- 1. Therapeutic Education Program (TEP)

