### Exclusion criteria

The patient will not be included for the following reasons:

- Patient with an atypical non-idiopathic Parkinsonian syndrome (such as Progressive Supranuclear Palsy (PSP), Multiple System Atrophy (MSA), Corticobasal Degeneration (CBD), etc.);
- Patients with a Parkinsonian syndrome induced by a drug;
- Patient already included in a clinical trial at the time of the study;
- Patient at a Hoehn and Yahr stage of 5;
- Patient with a severe or progressive psychiatric illness or dopaminergic psychosis currently considered as being progressive;
- Patient having undergone deep brain stimulation within the last 3 months or planning to have one during the year;
- Patient incapable of understanding the protocol, filling in a notebook or any other assessment criterion or of following the clinical trial procedures;
- Patient with cognitive decline that could interfere with the assessment;
- Patient under temporary guardianship/full guardianship/judicial protection.
  1. Number of subjects required

If we want a power of 80% for a difference of 4 points in quality of life (PDQ-39), given a standard deviation of 17 points and a level of 5% in a one-tailed test, we must recruit 111 Parkinson’s patients given a correlation coefficient of 50% between the answers for the two periods. Given the potential withdrawals from the trials, we will recruit 120 patients.

The number of subjects was calculated using data from a study using the PDQ-39 quality of life scale on Parkinson’s patients (Brefel-Courbon et al., 2003).

- 1. Recruitment methods

Patients with Parkinson’s disease will be selected at the Neurology consultation services at the 2 hospitals in Toulouse (Purpan and Rangueil) by neurologists specialized in caring for Parkinson’s patients ([name], [name], [name], [name]) or at the movement disorder unit of the Neurology service at Purpan Hospital. This study seeks to be pragmatic, so we will propose this study consecutively and not selectively to all Parkinson’s patients meeting the inclusion and exclusion criteria.

We expect an average recruitment of 5 to 10 patients a month. The duration of inclusion should be 24 months.

- 1. Randomization

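### The 111-patient calculation is a within-patient formula applied to a two-group trial: power for 4 points is about 36% (44% with baseline adjustment), not 80%

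*Protocol*

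**What the plan says.** Under Number of subjects required (Methodology), the protocol asks for "a power of 80% for a difference of 4 points in quality of life (PDQ-39), given a standard deviation of 17 points", at "a level of 5% in a one-tailed test". It concludes that "we must recruit 111 Parkinson’s patients given a correlation coefficient of 50% between the answers for the two periods", and it recruits 120 to allow for withdrawals. No formula is named and no withdrawal rate is given; going from 111 to 120 implies 9/120 = 7.5%.

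The design is described elsewhere. The Experimental plan calls the trial a "comparative prospective study of 2 groups of Parkinson’s patients", and the Randomization section assigns each patient to one group only, education programme or usual monitoring. The abstract (Methods and tools) plans quality-of-life assessment at 6 and 12 months "in 120 Parkinson’s patients (60 in each group"). Under Data analysis, quality of life is to be analysed by a linear model with a fixed treatment effect. A baseline covariate is not mentioned, and neither is a way of combining the two follow-up visits.

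**The concern.** A correlation between two periods, together with a total of 111, points to a formula in which each patient is compared with himself or herself. In this trial no patient receives both conditions. The main objective is a contrast between two independent groups, and the variance of that contrast is 2 × SD² / n per group. A within-patient formula leaves that factor out and so gives far too small a sample.

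This is the protocol's only power statement, and it supports the primary outcome. If it is wrong, the trial is likely to miss the benefit it was designed to find, and a null result could be read as evidence that the programme does not work.

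**Working it through.** **Inputs, all from Number of subjects required unless noted**
- Difference to detect: 4 points
- SD: 17 points
- Correlation r: 0.5
- Level: one-sided 5% (z = 1.645)
- Power: 80% (z = 0.842)
- Allocation: 60 per group (abstract, Methods and tools)

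**1. Reproducing the protocol's figure**

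SD of a within-patient difference = 17 × √(2 × (1 − 0.5)) = 17.

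n = (1.645 + 0.842)² × 17² / 4² = 111.7.

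This matches the stated 111 (truncated). The two-sided version gives 142 and does not match.

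**2. Sample size for two parallel groups, same inputs**

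n per group = 2 × (1.645 + 0.842)² × s² / 4², where s is the SD relevant to the analysis.

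| Analysis | s | n per group | Total |
|---|---|---|---|
| Follow-up score alone | 17 | 223.3 → 224 | 448 |
| Change from baseline | 17 × √(2 × 0.5) = 17 | 224 | 448 |
| ANCOVA on baseline | 17 × √(1 − 0.25) = 14.72 | 167.5 → 168 | 336 |

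These totals are before any allowance for withdrawals.

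**3. Power with 60 per group**

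- Follow-up or change score: SE = 17 × √(2/60) = 3.10; power = Φ(4/3.10 − 1.645) = 36%.
- ANCOVA: SE = 14.72 × √(2/60) = 2.69; power = Φ(4/2.69 − 1.645) = 44%.

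**4. Power with 111 evaluable patients (55.5 per group)**

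- Follow-up or change score: 34%.
- ANCOVA: 42%.

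**5. Difference detectable with 80% power at 60 per group**

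- Follow-up or change score: 2.487 × 3.10 = 7.7 points.
- ANCOVA: 2.487 × 2.69 = 6.7 points.

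**6. Sensitivity**

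- Two-sided 5% test, 60 per group: 25% (follow-up or change score) and 32% (ANCOVA).
- If 111 were meant per group: 54% and 65%. The protocol fixes 120 in total, so this reading is not open anyway.
- If 17 is the SD of the change and not of a single score: the change-score power is still 36%, because the two SDs coincide at r = 0.5.
- For ANCOVA to reach 80% at 60 per group, s would have to be 4 / (2.487 × √(2/60)) = 8.81. That needs r = √(1 − (8.81/17)²), about 0.86, against the stated 0.5.

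**The case against.** Three points on the other side deserve weight.

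**The analysis is not fully fixed.** The protocol measures quality of life at both 6 and 12 months and names only a linear model with a treatment effect. Suppose the analysis used the mean of the two follow-ups adjusted for baseline, with all pairwise correlations equal to 0.5 (an assumption). Then s = 17 × √(0.75 − 0.25) = 12.02, SE = 2.19 and power at 60 per group is 57%, with 224 patients in total needed for 80%. On that reading it would no longer be true that the trial misses a 4-point effect more often than not. The protocol does not state this analysis, however, and 57% is still far below 80%.

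**The formula is inferred.** The protocol does not name one, so a within-patient calculation is the likely explanation, based on the numerical match and the reference to two periods. Other routes reach about the same number. Putting SD × (1 − r) = 8.5 into a two-group formula gives 112 in total, but that is not a valid variance. A per-group figure of 112, from s = 12.02, could also have been taken for the total. The error does not depend on which route was used: with a valid variance, none gives 80% power at 120 patients.

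**The consequence is partly a prediction.** The protocol says what would follow a positive result and is silent on a null one. That a null result would be misread is a risk, not something the document states.

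These points limit how the size of the shortfall should be worded. They do not rescue the 80% claim.

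**Conclusion.** The concern holds. The stated sample size does not give the stated power for the design described. With SD 17, r = 0.5 and a one-sided 5% test, 120 evaluable patients give 36% power for 4 points on follow-up or change scores and 44% with baseline adjustment. The 44% rests on a covariate that the protocol does not mention. With the withdrawals the protocol itself allows for, the figures fall to 34% and 42%. On these single-contrast analyses, power is about half of what is claimed. Even the most favourable reading considered, averaging both follow-ups with baseline adjustment, stays well short of 80%. The paragraph is wrong as written and must be corrected; an analysis plan cannot make 111 right for these inputs.

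**What to change.** Replace the sample size paragraph with the parallel-group calculation:

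- Delete the claim that 111 patients give 80% power.
- State that 120 patients (60 per group) give about 36% power for 4 points without baseline adjustment and about 44% with it (SD 17, r = 0.5, one-sided 5%). Add that these become 34% and 42% with 111 evaluable patients.
- State the difference detectable with 80% power: about 7.7 points unadjusted, or about 6.7 points with ANCOVA. Quote the ANCOVA figures as the trial's own only if the analysis section is made to say that baseline is a covariate.
- State that a non-significant result will be reported with its confidence interval and not as absence of benefit. With ANCOVA the two-sided 95% half-width is about 1.96 × 2.69 = 5.3 points.

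The cost is amendment wording and a less favourable power statement, which the ethics committee will see. The correction adds no patients, visits or procedures. If the sponsor wants 80% power for 4 points, the totals above (448, or 336 with ANCOVA) show what that would take; enlarging the trial is a separate decision.

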### Follow-up and end-of-study visits

Patients will be assessed during a normal neurology follow-up consultation at 6 and 12 months after their inclusion.

During these 2 visits, the patient:

- will receive a neurological examination with a motor rating;
- fill in the self-assessment questionnaires;
- return the completed notebook and receive the notebook for the next visit (for the visit at 6 months).
  1. Data analysis

Data will be saved using the SAS software. The data input form will correspond exactly to the paper form used for gathering data.

The data will be made anonymous before its collation.

The statistical analysis will be descriptive as well as inferential:

- Qualitative variables will be described by presenting the frequency of each modality of these variables. Quantitative variables will be analyzed to establish the median, mean, standard deviation and extreme values.

- Quality of life will be analyzed classically using a linear model including a fixed treatment effect.

Comparisons of the medical costs, motor and psychological symptomatology (secondary quantitative assessment criteria) between two treatments will also be carried out in accordance with the process described above.

1. Expected consequences of the results of the project

If the impact of a TEP program is positive in terms of quality of life and if it does not produce additional costs, this type of care will be generalized for Parkinson’s disease and will give rise to contributions at national and international conferences.

1. Provisional schedule

Start of inclusions September 2008

End of inclusions September 2010

End of patient follow-up September 2011

Analysis of the results December 2011

1. Regulatory and ethical aspects

In accordance with law No. 2004-806 of 9 August 2004 relative to public health policy and its implementing orders, the project comes within the framework of an assessment of intermediate care and the study is subject to the opinion of a CPP (Comité de Protection des Personnes Sud-ouest et Outre-Mer – Institutional Review Board of the Southwest and Overseas Possessions). The research will not be implemented until a favorable opinion is received from the CPP.

All the information gathered is confidential and cannot be disclosed. The participants will be assured that the anonymity of each subject participating the study is guaranteed. No information that can be used to identify people will be transmitted to third parties other than those representing the sponsor and the Ministry of Health, who are authorized under the regulations to hold such information (and are bound by professional secrecy requirements).

Information gathered during this study will undergo data processing. An application for an authorization for automated data processing in research in the healthcare field will be filed with the CNIL (Commission Nationale de l'Informatique et des Libertés – French National Data Protection Authority).

Subjects will be informed of the study objectives and their rights to refuse participation. As this study comes under the framework of the assessment of intermediate care, its conduct and the subject’s participation or non-participation will in no way affect his/her usual care. Furthermore, in accordance with article 3 of the decree of 9 March 2007, the subjects will be informed of the study by a patient information letter and can manifest their opposition to participate in the study. They will be asked to sign a participation agreement.

After the start of the trial, any substantial modification thereto must be submitted to the study leader, who must obtain a favorable opinion from the CPP prior to implementation.

1. Bibliography

**-** De Boer AGEM, Wijker W, Speelman JD, de Haes JCJM**.** Quality of life in patients with Parkinson’s disease: the development of a questionnaire*. J Neurol Neurosurg Psychiatry* 1996; 61: 70-74.

**-** Carrère MO. La qualité de vie liée à la santé et l’évaluation économique. Journal d’Economie Médicale 1997; 15: 5-8.

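### The quality-of-life model names treatment as its only term, although baseline PDQ-39 is measured before randomization and the sample size relies on a 0.5 correlation: precision is given up that a baseline covariate would recover

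*Protocol*

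**What the plan says.** Four places in the protocol bear on this.

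- **Data analysis (Methodology).** "Quality of life will be analyzed classically using a linear model including a fixed treatment effect". No baseline term, change score, visit term or time point is named here or elsewhere. The next sentence says that comparisons of medical costs and of motor and psychological symptoms "will also be carried out in accordance with the process described above".
- **Experimental plan (Methodology).** In both groups "patients will undergo a clinical assessment before randomization and after 6 and 12 months of inclusion". The visit table places the self-assessment questionnaires at all three visits.
- **Inclusion visit.** The questionnaires and the UPDRS are done at inclusion, and the Randomization section places randomization after that visit. Baseline values of PDQ-39, SF-36, HAD, SAS-SR and UPDRS are therefore planned for every patient.
- **Number of subjects required.** The calculation targets 4 PDQ-39 points with 80% power, "given a standard deviation of 17 points and a level of 5% in a one-tailed test", and concludes that "we must recruit 111 Parkinson’s patients given a correlation coefficient of 50% between the answers for the two periods". Which two periods are correlated is not said.

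**The concern.** The design collects a pre-randomization value of the primary outcome, and the sample size uses a within-patient correlation. The model as written has no term through which that correlation can act. Baseline PDQ-39 is likely to be among the strongest predictors of follow-up PDQ-39, and entering it as a covariate is the usual way to gain from it.

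What is at stake is the width of the confidence interval and the power for the primary outcome, and likewise for the secondary scales analysed by the same process. A secondary matter is chance imbalance. The Randomization section describes no stratification, and eligibility runs up to Hoehn and Yahr stage 4, with or without deep brain stimulation, so some baseline difference between arms should be expected. An unadjusted estimate carries part of it.

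**Working it through.** **Inputs.** From Number of subjects required: difference 4, SD 17, one-sided 5%, power 80%, r = 0.5, so z = 1.645 + 0.842 = 2.486. From the abstract: 60 patients per arm. Assumption: r is the baseline to follow-up correlation and the SD is 17 at both times.

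**1. The protocol's own figure.** A one-group paired formula gives

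n = [17 × √(2(1 − 0.5)) × 2.486 / 4]² = [17 × 1 × 2.486 / 4]² = 111.67,

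which matches the stated 111 apart from rounding. The two-arm formulas tried do not match it: a comparison of follow-up scores needs 2 × (17 × 2.486 / 4)² = 223.3, so 224 per arm. The 111 therefore appears to rest on a within-patient difference.

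**2. Residual SD under three analyses.**

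- Treatment only, follow-up scores: SD = 17.
- Change from baseline: SD = 17 × √(2(1 − r)). At r = 0.5 this is 17, so nothing is gained.
- Treatment plus baseline covariate (ANCOVA): SD = 17 × √(1 − r²). At r = 0.5 this is 17 × √0.75 = 14.72, a 25% cut in variance.

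Since 1 − r² = (1 − r)(1 + r) and 1 + r is below 2 for any r below 1, ANCOVA has a smaller variance than change scores at every such r.

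**3. Power for 4 points, 60 per arm, one-sided 5%.** Power = Φ(4 / (SD × √(2/60)) − 1.645).

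- Treatment only: 4 / (17 × 0.1826) = 1.289, so Φ(−0.356) = 36%.
- ANCOVA, r = 0.5: 4 / (14.72 × 0.1826) = 1.488, so Φ(−0.157) = 44%.

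| r (0.5 stated; others assumed) | Treatment only | Change score | ANCOVA |
|---|---|---|---|
| 0.3 | 36% | 29% | 38% |
| 0.5 | 36% | 36% | 44% |
| 0.7 | 36% | 51% | 56% |
| 0.8 | 36% | 65% | 69% |

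With 111 evaluable patients (55.5 per arm), the r = 0.5 row becomes 34% for treatment only and 42% for ANCOVA.

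**4. The same gain in other units, at r = 0.5.** Patients required per arm fall from 224 to 168. The difference detectable with 80% power at 60 per arm falls from 7.7 to 6.7 points. With the covariate, 120 patients give the precision of 120 / 0.75 = 160 without it.

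**5. Chance imbalance.** The SE of the baseline difference is 17 × √(2/60) = 3.10. The probability of a difference of at least 4 points in either direction is 2 × (1 − Φ(4/3.10)), about 20%. At r = 0.5, a 4-point imbalance moves the unadjusted estimate by about 0.5 × 4 = 2 points.

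**The case against.** The strongest reply is that the sentence says the model includes a treatment effect, not that it contains nothing else. It does not define the response, and covariates are commonly settled in a statistical analysis plan, which is not at hand. A reader might infer that the protocol rules baseline out or throws it away; the text does not support that. It is silent on baseline. What stands is narrower: treatment is the only term named, and the sample-size paragraph uses a correlation that the named model does not.

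A second reply is that the response might be change from baseline, which would use the baseline. At the protocol's own r = 0.5 this gains nothing. Above 0.5 it does gain, and at r = 0.7 it captures most of the benefit (51% against 56%), so it would be wrong to say that change scores never help. A repeated-measures model with baseline among the outcomes would also use the correlation.

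Third, the unadjusted comparison is valid. In a randomized trial it is unbiased and keeps its type I error, and its standard error already allows for chance imbalance. A reader might take the 20% figure in step 5 as evidence of bias; it is ordinary sampling variation. This objection stands in full and limits the point to precision.

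Fourth, the baseline to follow-up reading of the 0.5 is natural but not stated, so the 25% and the 44% depend on it. This also stands, and is why a range is shown.

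**Conclusion.** The point holds as a loss of precision that can be recovered at almost no cost. If the stated 0.5 is the correlation of baseline with follow-up PDQ-39, the covariate is worth a 25% cut in residual variance and about 8 percentage points of one-sided power at 60 per arm (36% to 44%). The gain is about 2 points at r = 0.3 and 20 at r = 0.7.

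Two stronger conclusions should not be drawn. Leaving baseline out does not bias the comparison. Nor would putting it in rescue the planned power: 44% is still far below 80%, because 111 is reproduced by a one-group paired formula, while a two-arm comparison needs about 448 patients in total without the covariate (2 × 224) or 336 with it (2 × 168). That is a separate sample-size error and should be dealt with as such.

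For costs, the point does not apply in the same way. The healthcare notebook is handed out at inclusion, and the Costs section limits insurance-fund data to the period of the protocol, so no baseline cost is being left unused.

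**What to change.** In Data analysis, define the response and its visit, and write the model as follow-up PDQ-39 = treatment + baseline PDQ-39. State the same baseline-adjusted form for SF-36, UPDRS, HAD and SAS-SR, each with its own baseline value. In Number of subjects required, say which two periods the 0.5 refers to and base the calculation on that two-arm model.

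A repeated-measures mixed model of months 6 and 12 with baseline is a reasonable option but is not needed to meet this point. Pre-inclusion cost data should not be requested for it; that would be new personal-data collection outside the planned extraction.

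The change to the analysis is a sentence or two and needs no extra data, because the baseline scales are already collected. Aligning the sample-size paragraph means redoing that calculation. Should the change count as a substantial modification, the protocol's own rule requires a favorable ethics committee opinion before it takes effect.

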### Main criterion

**Self-assessment questionnaire on quality of life specific to Parkinson’s disease**

Quality of life will be assessed using a specific scale (PDQ-39).

We will use the specific self-assessment measurement questionnaire, PDQ-39 (Parkinson's Disease Quality of Life) (De Boer et al., 1996). Its specific indicators are suited to detecting observable variations in the quality of life for a given disease, and in principle cannot be used to make comparisons between care programs that address different diseases (Carrere, 1997). The PDQ-39 is made up of 39 health-related questions that are to be answered retrospectively over a period of 1 month using 5 levels of frequency (always, often, sometimes, rarely, never). This specific quality of life measurement instrument assesses 8 dimensions of Parkinson’s patients’ health: mobility, everyday activities, emotional well-being, psychological stress, social support, cognitive disorders, communication and physical discomfort.

- 1. Secondary criteria

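### The PDQ-39 model names treatment as its only term, although each patient gives a baseline, a month-6 and a month-12 score and withdrawals are expected; a baseline-adjusted repeated-measures model should replace it

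*Protocol*

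**What the plan says.** The protocol's Experimental plan sets three assessments: "In both groups, patients will undergo a clinical assessment before randomization and after 6 and 12 months of inclusion". The visit table there lists the self-assessment questionnaires at all three visits, so each patient who completes the study gives three PDQ-39 scores, two of them after randomization.

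Under Data analysis, the inferential plan for this main criterion is one sentence: "Quality of life will be analyzed classically using a linear model including a fixed treatment effect". Treatment is the one term it names. It mentions no baseline score, visit, patient effect or covariance structure. Neither this section nor the Main criterion section names the visit or summary that decides the trial. The next sentence extends the same process to costs and to motor and psychological symptoms.

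The section Number of subjects required relies on correlation within patients, "given a correlation coefficient of 50% between the answers for the two periods", without saying which two periods are meant. It also expects losses: "Given the potential withdrawals from the trials, we will recruit 120 patients".

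**The concern.** The stated model does not match the data that the design produces. A classical linear model with a fixed treatment effect is most naturally read as ordinary least squares with independent errors. Applied to this design, two direct uses have drawbacks:

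- **Both follow-up visits entered as independent rows.** The standard error is too small and the false-positive risk of the main test exceeds the stated 5%.
- **One visit fitted with treatment alone.** The baseline score, which would sharpen the comparison, is not used. A patient seen at month 6 but lost before month 12 contributes nothing to the month-12 comparison. If loss depends on how patients were doing at month 6, and differs between groups, the estimate is biased.

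The trial is open and only one group has regular program contact, so unequal loss is plausible, though the protocol gives no figures on it. At stake is the comparison that is meant to support wider use of the program.

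**Working it through.** **Inputs from the protocol.** 60 patients per group; SD 17; difference 4 points; one-tailed 5%; 80% power; correlation 0.5 between two unnamed periods; 111 patients raised to 120, an allowance of 9/120 = 7.5%.

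**1. The plan's own figure, and what its 0.5 refers to.** SD of a within-patient difference = 17 × √(2 × (1 − 0.5)) = 17. Paired one-group formula: n = (17 × (1.645 + 0.842)/4)² = 111.67, which matches the stated 111 within rounding. The two-arm formulas tried do not give 111. So the 0.5 more likely links baseline and follow-up than months 6 and 12. The month-6/month-12 correlation ρ is therefore an assumption, shown below as a range. (Whether a paired formula suits a two-arm trial is a separate matter.)

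**2. If both visits were pooled as independent.** At ρ = 0.5:

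- Model SE = 17 × √(2/120) = 2.19.
- True SE = 17 × √((1 + 0.5)/2) × √(2/60) = 2.69.
- Ratio = 1/√(1 + ρ) = 1/√1.5 = 0.816.
- True level = Φ(−1.645 × 0.816) = 9.0%. A simulation of 40,000 trials gave 8.7%.

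| Assumed ρ | SE too small by | True one-tailed level |
|---|---|---|
| 0.3 | 12% | 7.5% |
| 0.5 | 18% | 9.0% |
| 0.7 | 23% | 10.4% |
| 0.9 | 27% | 11.6% |

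The damage comes from the unmodelled patient correlation. With balanced visits, a missing visit term does not by itself bias the treatment contrast.

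**3. If month 12 alone were fitted.** Simulation of 4,000 trials per scenario: 60 per group, SD 17, all three correlations 0.5, true benefit 4 points at both visits. Assumed loss after month 6 has log-odds +1 per SD worse at month 6. The loss rates are assumptions; the protocol gives none.

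| Loss (control / program) | Treatment alone | With baseline | Using month 6 as well |
|---|---|---|---|
| 16% / 4% | 3.1 | 3.5 | 3.9-4.0 |
| 4% / 16% | 4.8-4.9 | 4.4 | 4.0 |
| about 9-10% each | 3.9-4.0 | 3.9-4.0 | 3.9-4.0 |

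Unequal loss of 16% and 4% averages 10%, or 12 of 120 patients, somewhat above the allowance of 9.

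**4. Effect on the test.** With no true effect and 16% / 4% loss, the bias is about 0.87 points against the program with treatment alone (sampling SD 3.31) and 0.47 with baseline (SD 2.87). One-sided rejection was 2.7% and 3.6%. Swapping the groups mirrors this: Φ(−(1.645 − 0.87/3.31)) = Φ(−1.38), about 8%, with treatment alone, and Φ(−(1.645 − 0.47/2.87)) = Φ(−1.48), about 7%, with baseline.

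**5. Does the repeated-measures model need baseline?** Root mean squared error for the month-12 contrast at 16% / 4% loss: month 12 with treatment alone 3.4; month 12 with baseline 2.9; both visits without baseline about 3.2-3.3; both visits with baseline about 2.87. Without baseline, the repeated-measures model is less accurate than simple baseline adjustment at month 12. With it, the two are about equally accurate and the bias is removed.

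**The case against.** A reader might infer that the protocol plans to treat 240 scores as independent, with a standard error 18% too small by its own correlation. The text does not support that. The word introducing the treatment effect is open-ended, so further terms are not excluded. Pooling is stated nowhere. A patient-level mean of the two visits, a change score, a baseline-adjusted fit or a repeated-measures model would all be compatible with the sentence. The 0.5 is not identified as the month-6/month-12 correlation, and step 1 suggests that it is not. Visit terms and covariance structure are also commonly left to a statistical analysis plan, which may exist but was not available. These points stand, and they make every figure above conditional.

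The unequal loss is likewise assumed. With equal score-dependent loss there is almost no bias, so it would be wrong to say that a single-visit fit is biased whenever sicker patients leave more often.

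It can also be argued that the bias runs against the program and so cannot produce a false claim of benefit. That is true only of the 16% / 4% pattern. Reversed, the benefit is overestimated and the false-positive risk rises.

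The objection does not remove the core. The protocol chose to state a model for its main criterion, and the model as stated has no named place for the baseline score or the second follow-up score.

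**Conclusion.** The point holds as a choice of method that should be improved, not as a proven error in the planned test. A baseline-adjusted repeated-measures model suits this design better than the model as stated, at almost no cost.

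The size depends on how the sentence would be applied. Pooling as independent understates the standard error by 12% to 27% for ρ from 0.3 to 0.9. A month-12 fit with treatment alone gives about 3.1 or about 4.9 instead of 4 when score-dependent loss is 16% against 4% in one direction or the other, and close to 4 when loss is equal. It also forgoes the precision that baseline offers. These results rest on assumed correlations and loss rates. Confidence is moderate, because a statistical analysis plan may already settle the matter.

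**What to change.** Replace the quality-of-life sentence in Data analysis with:

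> PDQ-39 at 6 and 12 months will be analysed in one linear mixed model with treatment, visit, treatment-by-visit, baseline PDQ-39 and baseline-by-visit as fixed effects and an unstructured within-patient covariance, keeping every patient with at least one follow-up score; the main test is the treatment contrast at one visit named in advance (for example month 12, the end of the program).

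Use the same model for the secondary scales measured at each visit (SF-36, HAD, SAS-SR, UPDRS). Costs keep one value per patient.

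The cost is one sentence in the protocol, the matching text in any statistical analysis plan, and a different procedure in the SAS software already planned. No extra patients or data are needed. The model assumes that data are missing at random given the observed scores, which is weaker than what a complete-case fit of one visit assumes. If loss proves small and equal between groups, it adds little beyond the baseline adjustment.
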